### Data analysis

#### Sample size calculation

The sample size required is based on an analysis using independent t-tests to test for differences between pairs of treatment groups, with alpha set at 0.05. Three comparisons will be made: the SNAG group compared to the placebo group, the Maitland mobilisation group compared to the placebo group and the SNAG group compared to the Maitland mobilisation group. Sample size calculations were based on a difference between the two groups that would be clinically significant for the main outcome measures, supported by the results of previous research where applicable data existed, and clinical expectations for those factors for which no previous data existed. This was estimated by biostatisticians from the Centre for Clinical Epidemiology and Biostatistics, The University of Newcastle, using other studies with the DHI and VAS as outcome measures 
[41,49,51,52]. The DHI was the primary outcome measure used for sample size calculations, as it is a widely reported measure of self-perceived disability and effect of dizziness on function. It has been shown to have strong validity and short-term test-retest reliability and good internal consistency 
[53,54]. Visual analogue scales have also been used in many studies to measure pain and the main complaint 
[49] and been shown to have high reliability and validity, and a calculation of sample size was also based on VAS data.

Assuming that the standard deviation of DHI scores is 15, then 30 participants per group will give the study 80% power to detect a difference of 11 units between groups for each comparison. Thirty participants per group are also required based on a 0–10 VAS scale (e.g. for dizziness), with a standard deviation of 2.4 and a clinically significant difference of 2 units with a power of 80% and a 5% confidence level.

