### Participants and recruitment

Ninety participants with cervicogenic dizziness will be recruited in the Hunter region of NSW, Australia, via media releases and resulting radio interviews and newspaper articles, by advertisements in local newspapers, and by referral from medical practitioners including neurologists (Figure 
1 Flow chart). Inclusion and exclusion criteria are summarised in Table 
1.

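### The VAS sample size does not follow from its printed inputs: they need 24 per group, not 30, and 30 gives about 89% power; the DHI figure is right but has no margin

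*Protocol article*

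**What the plan says.** The Sample size calculation section sizes the trial "based on an analysis using independent t-tests to test for differences between pairs of treatment groups", at an alpha of 0.05. It makes two power statements.

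- **DHI.** The assumed SD is 15, and the article concludes: "then 30 participants per group will give the study 80% power to detect a difference of 11 units between groups for each comparison".
- **VAS.** On a 0–10 scale, the same 30 per group is said to be needed as well, "with a standard deviation of 2.4 and a clinically significant difference of 2 units with a power of 80% and a 5% confidence level".

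Under Participants and recruitment, "Ninety participants with cervicogenic dizziness will be recruited". With equal allocation to three groups (Randomisation section) that is exactly 30 each. Outcomes are measured up to one year after treatment (Outcome measures section). The article prints no loss rate and no inflation for loss. It does not say whether the tests are one-sided or two-sided.

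**The concern.** The two calculations use different standardised differences: 11/15 = 0.733 for the DHI and 2/2.4 = 0.833 for the VAS. Test, alpha and power are the same, so they cannot both lead to 30 per group. One of the figures must be wrong, or must rest on an input that is not shown.

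The article presents the two outcomes as needing the same number for the same power. A reader would take the VAS, which the Primary outcome section uses for dizziness severity, to be powered at 80% with nothing to spare. A reader would also not see that room for loss to follow-up exists for one outcome and not for the other. The Sample size calculation section names the DHI as the measure used for sizing.

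**Working it through.** **Inputs, all from the Sample size calculation section:** independent t-test between two groups; alpha 0.05; power 80%; DHI SD 15, difference 11; VAS SD 2.4, difference 2. Allocation is equal. Two-sided testing is my assumption.

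**Formula.** Normal approximation: n per group = 2 × (1.960 + 0.842)² × (SD/difference)², where 2 × (1.960 + 0.842)² = 15.70. The t-test figures use the noncentral t distribution.

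**Step 1: reproduce the DHI figure.**
- Normal: 15.70 × (15/11)² = 29.2, so 30.
- t-test: n = 30.2. Power at 30 per group is 79.8% (81.1% by normal approximation).
- The stated 30 per group for 80% power reproduces.

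**Step 2: the same calculation for the VAS.**
- Normal: 15.70 × (2.4/2)² = 15.70 × 1.44 = 22.6, so 23.
- t-test: n = 23.6, so 24.
- Power at 30 per group is 88.8% (89.8% by normal approximation).
- With 30 per group, the difference detectable with 80% power is 1.77, not 2.
- The stated 30 does not reproduce.

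**Step 3: which inputs would give about 30 for the VAS?**

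| Change to the printed inputs | n per group (t-test) |
|---|---|
| One-sided test | 18 (normal approximation) |
| 20% loss added | 24/0.8 = 30 |
| 90% power | 31.3 |
| Alpha 0.05/3 | 31.6 |
| SD 2.72 | 30 |

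The first row moves further away. The article prints none of the others. The alpha split would also differ from the Statistical methods section, which uses ordered testing at the 5% level.

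**Step 4: margin if fewer than 30 per group are analysed.** The loss rates are assumptions, because the article gives none. The figures are for a t-test on completers at one time point.

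| Assumed loss | Analysed per group | DHI power | DHI difference at 80% power | VAS power |
|---|---|---|---|---|
| 0% | 30 | 79.8% | 11.0 | 88.8% |
| 10% | 27 | 75.3% | 11.7 | 85.2% |
| 15% | 25.5 | 72.8% | 12.0 | 83.1% |
| 20% | 24 | 70.1% | 12.4 | 80.7% |

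**The case against.** A reader might infer from Step 4 that the trial does not deliver the 80% power stated for the DHI. The documents do not support that, for three reasons.

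- The DHI sentence concerns 30 participants per group, and for 30 it is correct.
- The shortfall depends entirely on loss rates that the article does not give. An allowance may stand in the full protocol, which is not shown, and its absence from a journal article is not an error.
- The figures describe a completers t-test. The Statistical methods section plans generalized linear mixed models over all visits, with t-tests at each time point in addition. A mixed model uses the partial data of people lost later. As an illustration, adjustment for baseline with an assumed baseline-to-outcome correlation of 0.5 would give about 82% power at 24 per group, and 0.3 about 74%. The article states neither the correlation nor baseline adjustment, so this shows only that loss may be partly offset.

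It can also be said that the VAS error is harmless. It errs on the safe side, and the Primary outcome section names dizziness severity on the VAS as primary, so on the printed inputs the declared primary outcome has more power than claimed. The figure 30 may even contain an unprinted 20% allowance.

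These objections dispose of any claim of a demonstrated shortfall. They do not rescue the VAS sentence, which prints all its inputs except sidedness and then gives a number that does not follow from them under either choice. If 30 does include an allowance for loss, then the VAS figure counts people randomised and the DHI figure counts people analysed, and the article should say so.

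**Conclusion.** The VAS sample size is misstated. The printed inputs need 24 per group by two-sided t-test (23 by normal approximation); 30 per group gives about 89% power, or 80% power for a difference of about 1.8. This rests on the article's own figures and on two-sided testing; one-sided testing widens the gap.

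The DHI statement is correct, with one condition to be spelled out: its 80% power needs all 30 per group in the analysis. What happens with fewer is conditional (about 75% power at an assumed 10% loss and 70% at 20%, by completers t-test) and is not an established deficit. The point is a wrong figure in a conservative direction, with a note on the DHI. It gives no reason to enlarge the trial.

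**What to change.** Replace the VAS sentence with wording such as: *For the VAS (SD 2.4, difference 2 on a 0–10 scale; 24 mm and 20 mm on the 100 mm scale), 24 analysed per group are needed for 80% power by two-sided t-test at the 5% level. Thirty per group gives about 89% power with complete data and about 81% with 24 per group analysed.* If 30 came from a further input, such as an allowance for loss or a higher power, disclose that input instead. The millimetre values only match the scale in the Primary outcome section; the standardised difference is unchanged.

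Add to the DHI sentence that the 80% power assumes that all 30 per group are analysed. If a loss rate is quoted, mark it as an assumption and the resulting power as that of a completers t-test, and note that the planned mixed model may offset part of the loss.

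The cost is a few sentences. The 90 recruited, the design and the analysis stay as they are.

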#### Statistical methods

Biostatisticians from the University of Newcastle will guide and assist with the statistical analyses. Baseline characteristics will be summarized per group using the number of observations, mean, standard deviation, median, minimum and maximum for continuous measures and number of observations and frequency for categorical measures. Primary and secondary outcome measures are either continuous or ordinal in nature and will be analysed using generalized linear mixed models. As an example, for the primary outcome measure of the DHI, the outcome variable will be the DHI and the predictors will be time, treatment group and an interaction term for time by treatment group. The p-value for the interaction term will indicate whether there is a statistically significant difference in change in the DHI over time between the groups. We will use the ‘gate keeper’ approach to take account of the multiple testing and restrict the overall type I error rate to 5%. This means that we will test the SNAG intervention against the placebo first, then the Maitland mobilisation against the placebo and if those results are statistically significant at the 5% level we will then test the SNAG against the Maitland intervention. The primary and secondary outcome measures will also be compared between treatment groups at each time point using independent t-tests.

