**Methods:**

Participants with symptoms of dizziness described as imbalance, together with a painful and/or stiff neck will be recruited via media releases, advertisements and mail-outs to medical practitioners in the Hunter region of NSW, Australia. Potential participants will be screened by a physiotherapist and a neurologist to rule out other causes of their dizziness. Once diagnosed with cervciogenic dizziness, 90 participants will be randomly allocated to one of three groups: Maitland mobilisations plus range-of-motion exercises, Mulligan SNAGs plus self-SNAG exercises or placebo. Participants will receive two to six treatments over six weeks. The trial will have unblinded treatment but blinded outcome assessments. Assessments will occur at baseline, post-treatment, six weeks, 12 weeks, six months and 12 months post treatment. The primary outcome will be intensity of dizziness. Other outcome measures will be frequency of dizziness, disability, intensity of cervical pain, cervical range of motion, balance, head repositioning, adverse effects and treatment satisfaction. Economic outcomes will also be collected.

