#### Primary outcome

Severity of dizziness (an average level over the previous week) will be measured with a 100 mm horizontal visual analogue scale (VAS). The VAS has been used successfully to measure dizziness in other studies 
[4,37-39].

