#### Secondary outcomes

1) Frequency of dizziness will be measured on a six-point rating scale (0 = no dizziness, 1 = dizziness less than once per month, 2 = 1–4 episodes of dizziness per month, 3 = 1–4 episodes of dizziness per week, 4 = dizziness once daily, 5 = dizziness more than once a day or constant). This scoring method has been used by several researchers 
[4,8,37,38] to measure frequency of dizziness.

2) Disability caused by dizziness will be measured with the Dizziness Handicap Inventory (DHI). This is a health status measure specifically designed to assess dizziness. The DHI assesses the quality of life using three subscales evaluating the impact of dizziness on the functional, emotional and physical aspects of everyday life 
[40]. The highest possible score is 100, indicating maximum self-perceived handicap. The DHI has been shown to be a highly reliable and responsive tool 
[40-42].

3) Severity of neck pain (an average level over the previous week) will be assessed with a 100 mm VAS. There is much evidence supporting the high validity of the VAS for measuring pain intensity 
[43-47].

4) Global perceived effect will be used to assess satisfaction with treatment and measured by self-assessment on a six-point scale (0 = no benefit, 1 = minimal benefit, 2 = some benefit, 3 = a lot of benefit, 4 = great benefit, 5 = maximal benefit) as used in other studies 
[4,48,49].

5) Posturography will be used to identify and quantify disturbances in balance. Body sway will be measured with a Chattecx Balance Dynamic System (Serial No 1001, Chattecx Corporation, the Chattanooga Group, Tennessee). Recordings will be performed during the following tasks.

· standing erect with the neck in the neutral position with eyes open

· standing erect with the neck in the neutral position with eyes closed

· standing erect with the neck extended

· standing erect with the neck in left rotation

· standing erect with the neck in right rotation

· standing on a moving platform.

Posturography has been used in many studies to assess people with dizziness and has been found to have good correlations with the participant’s symptoms 
[4,6,8,37].

6) A Cervical Range of Motion (CROM) goniometer (Performance Attainment Associates, [name]), which has been shown to be a reliable tool with good validity 

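### The outcome sections make the dizziness VAS the only primary outcome, but the statistical methods call the DHI the primary, so the 5% gatekeeping sequence has no single stated outcome

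*Protocol article*

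**What the plan says.** Three places define the outcomes, and they agree with one another. The abstract states: "The primary outcome will be intensity of dizziness". The Primary outcome section contains one measure: "Severity of dizziness (an average level over the previous week) will be measured with a 100 mm horizontal visual analogue scale (VAS"). The Secondary outcomes section has, as its second item: "Disability caused by dizziness will be measured with the Dizziness Handicap Inventory (DHI").

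The Data analysis section labels the outcomes differently:

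- **Sample size calculation:** "The DHI was the primary outcome measure used for sample size calculations". The section supports this choice by pointing to the DHI's wide use, validity and reliability, and then adds a second calculation on a 0–10 VAS.
- **Statistical methods:** "As an example, for the primary outcome measure of the DHI, the outcome variable will be the DHI". This is the only outcome for which the mixed model is written out. The dizziness VAS is not named in this section.

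The same section then introduces a gatekeeping sequence to limit the overall type I error to 5%: SNAG against placebo, then Maitland against placebo, then SNAG against Maitland if those results are significant. The sequence orders treatment comparisons only. It does not say on which outcome they are tested.

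**The concern.** A confirmatory trial needs one stated outcome to which its error-rate claim applies. Here one can cite the abstract and the Primary outcome section for the VAS, or the Statistical methods section for the DHI, and nothing in the article reconciles them. If the two measures disagreed at the end of the trial, either could be presented as the planned primary result. The gatekeeping would not prevent this, because it controls error across group comparisons within an outcome and not across a choice between two outcomes. Placed directly after the DHI example, it could be read as applying to the DHI, whereas the outcome sections point to the VAS.

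**Working it through.** **1. Labels side by side**

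| Section | Dizziness VAS | DHI |
|---|---|---|
| Abstract, Methods | primary | not named |
| Primary outcome | primary (sole entry) | – |
| Secondary outcomes | – | item 2 |
| Sample size calculation | second calculation | primary measure for sizing |
| Statistical methods | not named | primary outcome measure |

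The Statistical methods row conflicts directly with the first three. The Sample size row is compatible with either reading (see the objection).

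**2. The plan's own sample-size figures**

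Inputs, all from Sample size calculation: "independent t-tests to test for differences between pairs of treatment groups, with alpha set at 0.05"; for the DHI, "Assuming that the standard deviation of DHI scores is 15" and "30 participants per group will give the study 80% power to detect a difference of 11 units between groups for each comparison"; for the VAS, SD 2.4, difference 2, 80% power and 30 per group. The section does not say whether the tests are one- or two-sided; two-sided is assumed.

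Normal approximation, with d = difference/SD:

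- n per group = 2 × (1.960 + 0.842)² / d² = 15.70 / d²
- power at n = Φ(d × √(n/2) − 1.960)

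DHI:
- d = 11/15 = 0.733
- n = 15.70/0.538 = 29.2, so 30. The t-test version gives 30.2.
- Power at 30: Φ(0.733 × 3.873 − 1.960) = Φ(0.880) = 81.1%. By t-test, 79.8%.
- The plan's 30 per group at 80% reproduces.

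VAS:
- d = 2/2.4 = 0.833
- n = 15.70/0.694 = 22.6, so 23. The t-test version gives 23.6, so 24.
- Power at 30: Φ(0.833 × 3.873 − 1.960) = Φ(1.267) = 89.8%. By t-test, 88.8%.

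So 30 per group is enough with either outcome as primary. The plan states 80% power for both outcomes; the figure of about 89% for the VAS is recomputed from its inputs.

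**3. What a free choice of outcome would do to the 5%**

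Take one group comparison at one time point with no true effect on either outcome, each tested two-sided at 5%. Let Z₁ and Z₂ be the two test statistics, bivariate normal with correlation ρ. The chance that at least one is significant is

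1 − P(|Z₁| ≤ 1.96 and |Z₂| ≤ 1.96) = 0.05 + 0.05 − P(both significant).

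The documents give no correlation between the VAS and the DHI, so ρ is assumed over a range:

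| ρ (assumed) | P(both significant) | False-positive rate |
|---|---|---|
| 0 | 0.0025 | 9.75% |
| 0.3 | 0.0049 | 9.5% |
| 0.5 | 0.0093 | 9.1% |
| 0.7 | 0.0165 | 8.3% |
| 0.8 | 0.0219 | 7.8% |
| 0.9 | 0.0296 | 7.0% |

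The rate never exceeds 10%, and it stays well above 5% even at high correlation.

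**The case against.** Several points against the concern have force.

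- **The sizing sentence is weak evidence.** It can mean only that the DHI was the main measure used for sizing. That reading is fair for that sentence. It does not rescue the Statistical methods sentence, which has no such qualifier.
- **The Statistical methods sentence is introduced as an example.** What it exemplifies is the model specification. The word primary is still attached to the DHI, so the conflict remains.
- **The sections meant to define outcomes agree.** This makes the VAS the better-supported reading and is why the fix follows it. It does not remove the contrary statement.
- **The error rates are illustrative.** They rest on assumed correlations and on a single test at one time point, whereas the main analysis is a group-by-time interaction in a mixed model. They apply only if the outcome is chosen after results are seen.

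A reader might also infer more than the article supports. One inference is that the trial was sized only on an outcome that is not its declared primary, and so may be too small for the VAS. The article gives a VAS calculation as well, and 30 per group exceeds the 24 that its inputs need. Another is that the plan intends different power for the two outcomes. It states 80% for both. A third is that the 5% claim has already failed. It is unsecured, because it would fail only if the choice of outcome depended on the data.

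**Conclusion.** The contradiction is real, and nothing in the article resolves it. It rests mainly on the Statistical methods section against the abstract, the Primary outcome section and the Secondary outcomes section; the sizing sentence adds some support. An article's brevity does not explain it, because the text states two incompatible things about the same choice.

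The consequence is that the 5% gatekeeping claim is attached to no single outcome. If the outcome were picked after seeing results, the false-positive rate for one comparison at one time point would be about 8.3% to 9.5%, with assumed correlation 0.7 to 0.3 and two-sided tests at 5%. The rate would be nearer 7% if the two measures correlate at 0.9. Sample size is not harmed. This should be corrected before analysis, because the choice could not later be shown to be independent of the results.

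**What to change.** Before any outcome data are compared by group:

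1. In Sample size calculation and Statistical methods, name dizziness severity on the VAS as the single primary outcome, as the abstract and the Primary outcome section already do.
2. State that the gatekeeping sequence runs on the dizziness VAS only.
3. Refer to the DHI as a secondary outcome throughout, and use the VAS for the worked model example or relabel the DHI example as secondary.
4. Base the sample-size statement on the VAS inputs (SD 2.4, difference 2; about 89% power by t-test at 30 per group). The DHI calculation (SD 15, difference 11, about 80% power) can stay as supporting information for a secondary outcome.

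The cost is wording only, with no additional participants. Giving the DHI a formal key-secondary rank would be a matter of preference and is not needed to remove the contradiction. The change fixes the outcome. It does not by itself settle how the interaction test and the t-tests at each time point relate, which is a separate question.

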### Study aims

The aim of this paper is to report the study protocol used to investigate the effectiveness of two manual therapy treatments in reducing the symptoms of cervicogenic dizziness and associated pain over 12 months. This will be investigated by comparing the effects of these treatments to each other and to a placebo intervention. Other aims of the study are: 1) to assess the effects of the interventions on cervical range of motion, head repositioning and balance; 2) assess and compare the cost effectiveness of the interventions; and 3) to report any possible adverse effects and treatment satisfaction.

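### The gatekeeping rule as written does not secure the stated 5% overall error, and on either reading it does not deliver 80% power for each comparison

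*Protocol article*

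**What the plan says.** All references are to the Protocol article.

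- **Statistical methods, purpose.** The gatekeeper is meant to "restrict the overall type I error rate to 5" per cent.
- **Statistical methods, rule.** The order of testing is given in one sentence: "This means that we will test the SNAG intervention against the placebo first, then the Maitland mobilisation against the placebo and if those results". The rest of that sentence makes SNAG versus Maitland depend on both placebo comparisons reaching significance at 5%. No alpha is split between the first two tests. The section closes by adding independent t-tests between the groups at every time point, with no condition attached.
- **Sample size calculation.** The three pairwise comparisons are sized as stand-alone t-tests, "with alpha set at 0.05". For the DHI with SD 15, "then 30 participants per group will give the study 80% power to detect a difference of 11 units between groups for each comparison".
- **Study aims.** The effectiveness question is to be answered by "comparing the effects of these treatments to each other and to a placebo intervention". The Abstract and Discussion also list SNAG versus Maitland as a comparison of interest.

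**The concern.** A fixed-sequence gatekeeper holds 5% only if each test is run after the one before it has succeeded. Here the conditional clause stands before the third test only, and its plural subject presupposes that both placebo results are already in hand. Nothing says that Maitland versus placebo waits for SNAG versus placebo. If it does not wait, two full 5% tests share one placebo arm and the promised error rate is exceeded.

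The power statement has a related problem. It treats each comparison as free-standing, whereas at least one of the three is conditional on others. A conditional test succeeds only when the earlier tests succeed too, so its power cannot exceed the stand-alone figure and may be far below it. The comparison affected on every reading is SNAG versus Maitland, which is an aim of the trial.

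**Working it through.** **Inputs.** 30 per group, SD 15, difference 11 (DHI), alpha 0.05 per test, from Sample size calculation. Equal allocation, from Randomisation. Two-sided testing is assumed, because sidedness is not stated. The effects of each treatment versus placebo are not given, so a range is shown.

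**1. The plan's own figure.** n per group = 2(1.960 + 0.842)² × 15² / 11² = 29.2, rounded up to 30. Normal-approximation power at n = 30: 11 / (15 × √(2/30)) = 2.84, and Φ(2.84 − 1.96) = 81.1%. Exact t-test power is 79.8%. The stated 80% reproduces for a single comparison tested alone.

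**2. Error, literal reading.** The two placebo contrasts share the placebo mean. Their correlation is (σ²/n) / (2σ²/n) = 0.5. Under no effect anywhere, P(at least one significant) = 1 − P(|Z₁| < 1.96 and |Z₂| < 1.96, correlation 0.5) = 9.07%. Simulated trials with t-tests at n = 30 give 9.06%. For reference, independent tests would give 1 − 0.95² = 9.75%. Each placebo comparison keeps its stand-alone power of 79.8%.

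**3. Strict fixed sequence.** Family-wise error is 5%. Maitland versus placebo now counts only if SNAG versus placebo is also significant. With both treatments 11 units better than placebo, P(both significant) = 68.4% by simulation.

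**4. SNAG versus Maitland, either reading.** The test counts only if all three tests are significant. The true SNAG–Maitland difference is 11 in every row (simulated, n = 30, SD 15):

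| Effect vs placebo: SNAG | Effect vs placebo: Maitland | Stand-alone power | Power under the rule |
|---|---|---|---|
| 11 | 0 | 80% | 1.9% |
| 16.5 | 5.5 | 80% | 17.8% |
| 22 | 11 | 80% | 60.7% |
| 33 | 22 | 80% | 79.7% |

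In the first row both placebo tests are significant in only about 3.4% of trials. The stated 80% is approached only when the weaker treatment beats placebo by about 22 units, twice the design difference.

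**5. Closed test for comparison.** A global 2-df test at 5% is followed, if significant, by all three pairs at 5%. Simulated family-wise error under no effect is 5.0%. SNAG versus Maitland power is 75% for effects of 11 and 0, 79% for 16.5 and 5.5, and 80% for 22 and 11. SNAG versus placebo at 11 units has 75% power when Maitland equals either placebo or SNAG, and 69% when Maitland lies midway at 5.5.

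**The case against.** The strongest reply is that the authors named a gatekeeper, stated its purpose and put the tests in order. Those words fit a fixed sequence with a loosely placed condition, and a fixed sequence holds 5%. That is a fair account of what may have been intended. It does not settle the matter, because the sentence that defines the rule omits the condition on which the control depends.

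Making the head-to-head wait until both treatments have beaten placebo is also a legitimate priority: it avoids ranking treatments not shown to work. This stands. The order is a choice, and the fault is the power claim attached to it.

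A reader might go further in four ways that the document does not support.

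- **That error is 9% and Maitland power is 68%.** These belong to readings that exclude each other. With 9% error both placebo comparisons keep about 80% power; with 68% power, error is 5%.
- **That SNAG versus Maitland goes untested when one treatment fails.** The t-tests at each time point are unconditional, so the two treatments are still compared. What is lost is the error-controlled test.
- **That the power claim is incoherent because three pairwise differences cannot all be 11.** The claim is about each pair separately and does not assume that all three hold together.
- **That the head-to-head has 2% power.** That is one scenario, with Maitland exactly equal to placebo, and the protocol states no such effect.

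Finally, the section already yields a three-group time-by-treatment interaction p-value. Used as a first hurdle, it would change the error calculation, but the text gives it no such role.

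**Conclusion.** The point holds in a limited form. The rule as written does not secure 5% overall error: on its literal wording the rate is about 9%, and on a strict sequence it is 5%. The text does not say which applies. On neither reading does 80% power hold for each comparison. The literal reading costs power for SNAG versus Maitland only. The strict sequence also takes Maitland versus placebo to about 68% when both treatments are 11 units better. The head-to-head figure of 2% to nearly 80% rests on assumed effects versus placebo.

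The calculations assume two-sided t-tests, normal data, 30 analysed per group and a common SD of 15. The 9% depends on equal allocation and the shared placebo arm, not on the SD or the choice of outcome. The power figures are for the DHI, the measure for which the claim is made.

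**What to change.** Before unblinding, state one rule that holds 5%. There are two sound options, and the choice between them is one of priority.

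1. **Write in the missing condition.** Maitland versus placebo is tested only if SNAG versus placebo is significant, and SNAG versus Maitland only if both are. This costs one clause. The price is the lower power for Maitland versus placebo and for the head-to-head shown above.
2. **Use the three-group closed test**, if the head-to-head aim should not depend on both treatments beating placebo. Test equality of the three groups at 5% (2 df); if significant, test all three pairs at 5% each. This needs one named primary contrast (one outcome, and one time point or summary over time), which the time-by-treatment interaction over repeated assessments does not supply by itself. The price is a fall in SNAG versus placebo power at 11 units from 80% to about 75% when the third arm matches one of the other two, and to about 69% when it lies midway.

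Under either option, restate power for each comparison with the assumed effects versus placebo set out, and label the time-point t-tests as outside the 5% control. Neither option in itself requires more participants, provided the restated power is accepted.
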